**Figure 1 figure1:**
[figure not shown]
Study design.

**Table 1 table1:** Description of the assessment of the study outcomes, all completed in French.

Outcomes			Assessment methods and tools	Number of assessments and timing
**Primary outcomes**				
	Feasibility		Refusal, recruitment, retention, attendance, attrition, and missing data rates tracking by study staff	Throughout the study
	Acceptability		Technical Quality Assessment Questionnaire Semistructured individual interviews Acceptability questionnaire developed by the study authors	9; immediately after each intervention session during phases B1 and B2 1; 1 to 4 weeks after phase B1 2; 1 to 3 days before and after phase B1
**Secondary outcomes**				
	**Behavior targeted: MVPA^a^ (primary outcome for a future large-scale trial)**			
		MVPA (min/days)	Accelerometer (Actigraph)	8; during the 7 or 14 days of the phase A1, during 7 days before phase B2, mid- and after phases B1 and B2, as well as 6 and 12 months after MBS^b^ (phase A3)
	**Generalization measures (secondary outcomes for future large-scale trial)**			
		Health-related quality of life	RAND 36-item health survey	10; 1 to 3 days before phase A1, 1 to 3 days before, mid- and after phases B1 and B2, as well as 1, 6, and 12 months after MBS (phase A3)
		Anxiety and depressive symptoms	PHQ-9^c^ GAD-7^d^	10; 1 to 3 days before phase A1, 1 to 3 days before, mid- and after phases B1 and B2, as well as 1, 6, and 12 months after MBS (phase A3)
		Motivational regulations for PA^e^	BREQ2^f^	6; 1 to 3 days before and after each phase
		Basic psychological needs satisfaction and frustration	BPNSFS^g^	6; 1 to 3 days before and after each phase
		Self-efficacy for PA	Self-efficacity scale to overcome PA barriers developed by the study authors following Bandura’s recommendations	6; 1 to 3 days before and after each phase
		PA enjoyment	PACES^h^	6; 1 to 3 days before and after each phase
		Social support for exercise	SSES^i^	6; 1 to 3 days before and after each phase
	**Covariables**			
		Sociodemographic data	Questionnaire developed by the study authors	1; 1 to 3 days before phase A1
		Smoking status	Self-reported	6; 1 to 3 days before and after each phase
		Alcohol consumption	AUDIT-C^j^	6; 1 to 3 days before and after each phase
		BMI and weight loss	Self-reported medical records	6; 1 to 3 days before and after each phase
		Medications and medical conditions	Medical records	6; 1 to 3 days before and after each phase
		Date and place of MBS	Self-reported medical records	1; at the end of the study
		Pain	RAND 36-item health survey (bodily pain subscale)	10; 1 to 3 days before phase A1, 1 to 3 days before, mid- and after phases B1 and B2, as well as 1, 6, and 12 months after MBS (phase A3)
		Sedentary time, time spent on light-intensity PA, and step count	Accelerometer (Actigraph) GPAQ^k^	8; during the 7 or 14 days of the phase A1, during 7 days before phase B2, mid- and after phases B1 and B2, as well as 6 and 12 months after MBS (phase A3) 10; 1 to 3 days before phase A1, 1 to 3 days before, mid- and after phases B1 and B2, as well as 1, 6, and 12 months after MBS (phase A3)
		Self-reported sitting time and MVPA (min/week)	Accelerometer (Actigraph) GPAQ	8; during the 7 or 14 days of the phase A1, during 7 days before phase B2, mid- and after phases B1 and B2, as well as 6 and 12 months after MBS (phase A3) 10; 1 to 3 days before phase A1, 1 to 3 days before, mid- and after phases B1 and B2, as well as 1, 6, and 12 months after MBS (phase A3)

^a^MVPA: moderate-to-vigorous intensity physical activity.

^b^MBS: metabolic and bariatric surgery.

^c^PHQ-9: Patient Health Questionnaire.

^d^GAD-7: Generalized Anxiety Disorder scale.

^e^PA: physical activity.

^f^BREQ-2: Behavioral Regulation in Exercise Questionnaire-2.

^g^BPNSFS: Basic Psychological Need Satisfaction and Frustration Scale.

^h^PACES: Physical Activity Enjoyment Scale.

^i^SSES: Social Support for Exercise Survey.

^j^AUDIT-C: alcohol use disorder identification test–concise.

^k^GPAQ: Global Physical Activity Questionnaire.

### Participants

Participants are adults residing in or around 3 cities (ie, Montreal, Quebec City, and Chicoutimi) in the province of Quebec (Canada) and receiving care at either one of 2 tertiary care centers (Institut Universitaire de Cardiologie et de Pneumologie de Québec-Université Laval and the Centre Intégré Universitaire de Soins et de Services de Santé [CIUSSS] du Nord-de-l’Île-de-Montréal) or at a regional center (CIUSSS du Saguenay–Lac-Saint-Jean). Recruited strategies include (1) placing posters in waiting rooms at the target centers and (2) asking health professionals from hospitals at each site to refer to potentially eligible patients. For the latter, health professionals will provide the research team with the name and contact information of patients who have a planned sleeve gastrectomy in >12 weeks and who have provided verbal consent to be contacted by the research team for information on the study. The target sample size will be 12 (approximately 4 per site), which is considered acceptable for a single-case experimental study with multiple base levels, as participants serve as their own control, and outcomes will be measured repeatedly across observational and interventional phases [75,77].

The inclusion criteria are (1) ≥18 years of age; (2) scheduled to undergo sleeve gastrectomy in >12 weeks in one of the 3 associated hospitals (University Institute of Cardiology and Pulmonology of Quebec, Quebec; Sacré Cœur Hospital, Montreal [CIUSSS du Nord-de-l’Île-de-Montréal]; Chicoutimi Hospital, Chicoutimi [CIUSSS Saguenay–Lac-Saint-Jean]) Qc, Canada); (3) self-report ≤150 minutes of MVPA per week; and (4) access to a computer with internet and an interface with a camera. Exclusion criteria are (1) having a contraindication to PA without medical clearance (the Get Active questionnaire from the Canadian Society for Exercise Physiology [78] is used to determine if medical clearance is needed); (2) already enrolled in a supervised exercise intervention or PA behavior change intervention; (3) inability to speak and understand French; and (4) need a wheelchair, cane, walker, or other support or supports to move.

### Measurements

#### Primary Outcomes

##### Feasibility

The feasibility of the protocol or methods will be assessed at the end of the study using the following criteria tracked by the study staff: (1) refusal rate (percentage of participants who declined to participate); (2) recruitment rate (number of participants recruited per month at each center, number of sleeve gastrectomies performed per month at each center during the recruitment period), and sources of referral (eg, professionals, and self via poster); (3) retention rate (percentage of participants who complete all assessments and interviews); and (4) percentage of missing data (overall or total, per participant, per outcome, and per assessment time point). The feasibility of the intervention will be assessed at the end of the study using the following data tracked by the study staff: (5) attendance rate (number of sessions completed by participants) and (6) attrition rate (percentage of participants who did not complete the intervention). In addition, the reasons for refusing to participate in the study, as well as the reasons for dropping out of the study and the intervention, are documented by study staff, when available, and will be reported at the end of the study.

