## Results

The study began in September 2021, and as of July 2022, 12 participants have provided informed consent and been enrolled. Data collection is expected to end in fall 2023, depending on the MBS date. Analysis of pre-MBS data is planned for fall 2022, with the manuscript expected to be submitted in spring 2023. Analysis of post-MBS data is planned for fall 2023, with a second manuscript expected to be submitted in spring 2024.

The achievement of the following criteria based on the literature [22,28,29,63,72,73,118] will be considered satisfactory: (1) refusal rate ≤20%, (2) recruitment rate ≥1.8 participants recruited per month, (3) retention rate after phase B1 (before MBS) ≥80%, (4) percentage of missing data after phase B1 (before MBS) ≤10%, (5) intervention attendance rate ≥80%, and (6) intervention attrition rate ≤20%.

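### Retention is defined as having no missed assessment, so the 80% criterion can fail with no dropouts and low missing data, and no thresholded rate measures staying in the study

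*Protocol article*

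**What the plan says.** The protocol article, Methods, Feasibility, lists six tracked measures. The third is "retention rate (percentage of participants who complete all assessments and interviews". The fourth is "percentage of missing data (overall or total, per participant, per outcome, and per assessment time point". The sixth, attrition, counts participants who do not finish the intervention. The same section says that reasons for leaving the study and for leaving the intervention will be documented where available and reported.

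The Results section sets the satisfactory levels. For these two measures they share a horizon: "retention rate after phase B1 (before MBS) ≥80%, (4) percentage of missing data after phase B1 (before MBS) ≤10" percent. It does not say which of the four missing-data denominators the 10% limit refers to.

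The sample size is stated under Participants: "The target sample size will be 12 (approximately 4 per site". Table 1 gives the assessment schedule. For the accelerometer it is "8; during the 7 or 14 days of the phase A1, during 7 days before phase B2, mid- and after phases B1 and B2", with two later windows. For the main questionnaires it is "10; 1 to 3 days before phase A1, 1 to 3 days before, mid- and after phases B1 and B2", with three later occasions. There is also one interview 1 to 4 weeks after B1, and an acceptability questionnaire before and after B1.

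**The concern.** Retention normally tells the planner of a larger trial what fraction of enrolled people will still be there at the endpoint. Here a person who attends every session, never withdraws and misses one assessment counts as not retained. The event is then counted twice, once under retention and once under missing data, with different tolerances. Attrition does not fill the gap, because someone can finish the six sessions and then leave the study, or stop the sessions and keep supplying data.

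Feasibility is a primary outcome, and retention is one of six published criteria for it. As defined, the criterion can return an unsatisfactory verdict when nobody has left and the data are nearly complete. If the figure is read by its label, it would overstate expected dropout in the future trial.

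**Working it through.** The 80% and 10% levels are taken from the literature, so there is no derived figure to reproduce. The check is whether the two criteria give compatible verdicts on the same data.

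**Inputs.** n = 12 (Participants). Assessments per person up to the end of B1, called k, are counted from Table 1:
- 4 questionnaire occasions: before A1, and before, mid and after B1
- 3 accelerometer windows: A1, mid-B1, after B1
- 1 interview
- 2 acceptability questionnaires

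The article does not say what unit an assessment is, so three counts are used: k = 4 (questionnaire time points only), k = 4 + 3 + 1 = 8, and k = 8 + 2 = 10. The last is the least favourable to the plan, because the acceptability forms share their 1-to-3-day windows with questionnaires already counted.

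**Number needed.** 0.80 × 12 = 9.6, so at least 10 participants must have nothing missing. 10/12 = 83.3% passes and 9/12 = 75% fails.

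**Smallest failing case (no missingness model needed).** Three participants miss one assessment each. Overall missing data = 3/(12k):
- k = 4: 3/48 = 6.25%
- k = 8: 3/96 = 3.1%
- k = 10: 3/120 = 2.5%

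All three are below 10%, and there are no dropouts.

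**Passing case at the limit.** Two participants each miss 60% of their data and the other ten miss nothing. Overall missing data = 2 × 0.60/12 = 10% and retention = 10/12 = 83.3%. Both criteria are met. The verdict therefore depends on how missingness is spread as well as on how much there is.

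**Illustration with scattered missingness.** Assume each assessment is missed independently with probability 0.05. Expected retention as defined is 0.95^k. The chance of passing is P(X ≥ 10) for X ~ Binomial(12, 0.95^k). The chance of meeting the 10% limit as an overall rate is P(Y ≤ 0.10 × 12k) for Y ~ Binomial(12k, 0.05), with the limit rounded down to 4, 9 and 12 missed assessments.

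| k | Expected retention | P(at least 10 of 12) | P(overall missing ≤ 10%) |
|---|---|---|---|
| 4 | 81% | 0.61 | 0.91 |
| 8 | 66% | 0.18 | 0.98 |
| 10 | 60% | 0.08 | 0.99 |

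**Missingness compatible with 80%.** Solving (1 − m)^k = 0.80 gives m = 1 − 0.80^(1/k): 5.4% for k = 4, 2.8% for k = 8 and 2.2% for k = 10. Under scattered missingness, the retention rule is stricter than the 10% rule at every count.

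**Same data under a still-in-study rate.** In the smallest failing case nobody has withdrawn, so that rate is 12/12 = 100%.

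**The case against.** The definition is explicit and published, so a reader can see what is counted. Retention counts people and missing data counts data; two measures at different levels may disagree without contradiction. Asking for complete assessments is a demanding bar, but a legitimate one. This stands as a reason not to call the definition an error or to discard it.

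Several stronger readings are tempting but not supported:

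- A reader might infer that the criterion will fail at acceptable missing-data levels. It can fail. People who disengage tend to miss several assessments, and the passing case above shows both criteria met at 10% missing.
- A reader might take the 0.08 chance as the size of the problem. It rests on the least favourable count and on independence; at k = 4 the chance is 0.61.
- A reader might infer that the two thresholds contradict each other outright. That assumes the 10% limit is the overall rate. Taken per participant with k = 8, one missed assessment is 1/8 = 12.5%, which also exceeds 10%, and the criteria then agree.
- A reader might infer that the decision on a larger trial hangs on this result. The Results section only calls attainment of the criteria satisfactory. It gives no stop/go rule and no requirement to meet all six.
- A reader might apply the all-or-none rule to the whole study, where it would be stricter still. The stated threshold "retention rate after phase B1 (before MBS) ≥80" percent confines it to the period up to B1.

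Because reasons for leaving the study are to be reported, a 75% figure with no dropouts would probably be noticed. That softens the risk of misleading the larger trial. It does not supply a study-retention rate, because a list of reasons, kept where available, is neither a rate nor measured against a threshold.

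**Conclusion.** The point holds in a limited form. Retention as defined is a complete-data rate, and none of the six thresholded measures captures remaining in the study. The criterion can fail with no dropouts at overall missing data of 2.5% to 6.25%, depending on the unit of assessment. That result is arithmetic and needs only n = 12, the count from Table 1, and the reading of "percentage of missing data after phase B1 (before MBS) ≤10" percent as an overall rate. The probabilities of passing (0.61, 0.18, 0.08) also assume 5% missingness and independence, and serve only as illustration. Effect estimates are not affected. The consequence is a possibly misleading verdict on one primary feasibility criterion, and a poor dropout figure for the next trial.

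**What to change.** In Feasibility and in the list of criteria in Results:

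1. Keep the prespecified figure, but label it the all-assessments-complete rate.
2. Add, as a dated change, a retention rate defined as the percentage of enrolled participants not withdrawn or lost at the end of B1.
3. Report both against 80%.
4. Use the still-in-study rate for dropout planning in the larger trial.

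Replacing the published definition outright would be the wrong course. All 12 participants were enrolled by July 2022 and the study is open label, so swapping in a more lenient rule would be a post hoc relaxation of a success criterion. Reporting both avoids that.

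The cost is small, since staff already track drop-out. The downside is a second figure to report. The added rate is more lenient and was introduced after enrolment, and the report must say so.

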##### Acceptability

Immediately after each intervention session, the PA counselor completes the technical quality assessment questionnaire to report their satisfaction with the quality and performance of the Zoom technology platform [79]. The questionnaire includes 5 items: the first 3 concern the technological difficulties encountered by the PA counselor, and the last 2 relate to audio and video difficulties experienced by the participant. A high score indicates a low occurrence of technical problems. The questionnaire is modified for the study by adding 3 questions to assess the PA counselor’s perceived quality of the relationship with the participant, whether they believed the intervention session goals were met, and their overall satisfaction with the intervention session, with response options ranging from 0 to 10 (from lowest to highest satisfaction rate).

The acceptability of the protocol or methods and intervention is assessed during semistructured individual interviews with participants conducted via the Zoom platform. Participants are asked about their perceptions, opinions, and experiences regarding the intervention and study protocol or methods (eg, positive and negative experiences, adverse events related to the intervention and study, barriers, facilitators, satisfaction, perceived benefits, and suggestions for improvement). In addition, participants complete a 7-item questionnaire with statements in the future tense for before phase B1 or past tense for after phase B1, developed by the study authors ([name], unpublished data, July 2022), with items covering the 7 concepts of the *Theoretical Framework of Acceptability* by Sekhon et al [80] (ie, affective attitude, burden, ethicality, intervention coherence, opportunity costs, perceived effectiveness, and self-efficacy).

#### Secondary Outcomes

##### MVPA (Primary Outcome for the Future Large-scale Trial)

Daily MVPA is directly assessed using a triaxial accelerometer worn at the hip on the right side (Actigraph wGT3X-BT) during phase A1 and then for 7 days during the other assessment time points (Figure 1). Participants are instructed to wear the accelerometer continuously, except during water-based activities, and to maintain a log of wear times with waking and bed times. Accelerometer data will be extracted and downloaded (10-second epochs) using Actilife version 6.13.4 and will be cleaned in accordance with the logbooks provided by the participants. Only data from participants who wear the accelerometer for ≥3 days (including at least 1 weekday and 1 weekend day) and ≥10 hours/day will be analyzed [18,81]. The nonwear time is defined as a period of ≥120 minutes of consecutive zeros [82]. Accelerometer data will be used to quantify the time spent in MVPA (min/day). As PA intensity classifications have not yet been established for adults undergoing MBS, existing threshold values for the general population will be used for analyses (moderate-intensity PA=1952-5724 and vigorous-intensity PA 5724 counts/min) [83].

Data gathered immediately after phase B1 will be used to estimate effect sizes to determine sample size calculation for a future large-scale trial. Achieving PA recommendations of ≥150 min/week of MVPA will be judged as clinically significant [84,85].

##### Generalization Measures (Secondary Outcomes for the Future Large-scale Trial)

As recommended in the study by Tate et al [75], generalization measures are administered to increase the external validity of the study [86]. Generalization measures are dependent variables measured in addition to the targeted behavior to assess whether the effects of the intervention will be generalized to other results in the scientific literature [87]. In this study, generalization measures are used to assess changes in several psychosocial factors related to PA, spanning SDT, SCT, and health.

Health-related quality of life is assessed using the generic *RAND*-36 questionnaire [88], a 36-item questionnaire evaluating 8 concepts: physical functioning, role limitations owing to physical health, role limitations owing to emotional problems, energy or fatigue, emotional well-being, social functioning, pain, and general health perceptions. In addition, the *RAND*-36 contains an additional item to assess the perceived change in health status. The overall physical and mental health scores will be calculated from the 8 subscales [88]. A 3- to 5-point increase in overall physical and mental health scores is considered clinically significant [89,90]. According to the literature, owing to the likely absence of weight loss associated with the pre-MBS intervention, a score of 3 will be used as the minimal clinically important difference (MCID) [28,91].

The severity of anxiety and depressive symptoms will be assessed using the Patient Health Questionnaire (PHQ-9) [92] and the Generalized Anxiety Disorder scale (GAD-7) [93] as recommended by Obesity Canada [8]. The PHQ-9 is a 9-item validated scale that assesses the intensity of depressive symptoms. The GAD-7 is a 7-item self-rating scale that assesses the severity of anxiety symptoms. The MCID for the PHQ-9 and GAD-7 [94], based on the range of baseline depressive or anxiety symptom severity, will be used. Then, the MCID range will be 0 to 10 points (10/21, 48%) on the GAD–7 and 0 to 14 points (14/27, 52%) on the PHQ-9 for participants with baseline very mild to high anxiety or depression symptoms [94].

##### Theoretical Construct Measures (Secondary Outcomes for the Future Large-scale Trial)

To explore whether the intervention can change one or several of the theoretical constructs targeted, several measures are used to assess SDT, SCT, and evidence-based PA determinants [54,95,96], including PA enjoyment, motivational regulations for PA, psychological needs satisfaction and frustration, self-efficacy to overcome barriers to PA, and social support for exercise. PA enjoyment is assessed using the 18-item PA Enjoyment Scale [97]; motivational regulations for PA (ie, intrinsic, identified, introjected, integrated, external, and amotivation) are assessed using the 19-item Behavioral Regulation in Exercise Questionnaire-2 [95]; basic psychological needs satisfaction and frustration (ie, perceptions of autonomy, relatedness, and competence satisfaction and frustration) are assessed using the 24-item Basic Psychological Need Satisfaction and Frustration Scale [98,99]; self-efficacy to overcome common barriers to PA is assessed using a 20-item questionnaire developed by the research team according to Bandura’s recommendations. Participants are asked about their confidence to engage in PA 3 times per week in the presence of 20 different types of conditions using a 0% (“not confident at all”) to 100% (“highly confident”) scale [100], and perceived social support for PA received from family and friends is assessed using the 26-item Social Support for Exercise Scale [101,102]. Each measure will be scored following the scoring procedures, wherein higher scores will reflect greater PA enjoyment, intrinsic, identified, introjected, integrated, external, amotivation, self-efficacy to overcome common barriers to PA, psychological needs satisfaction, psychological needs frustration, and perceptions of social support for exercise.

